### 2.3. Sample Size Calculation

The sample size was determined using Encyclopaedia Medical Statistics 3.2 software (PEMS 3.2, Guangzhou Jing far Pharmaceutical Research Co., Ltd., Guangzhou, China) with 90% power and a significance level of 0.05 (two-sided). According to Lizogub et al. [30], the sample size should consist of 50 participants in each group. Considering the potential 20% loss, 60 participants are needed for each group. As there is a low-dose group, a middle-dose group, a high-dose group, and a control group with five centers involved, a total of 240 participants will be recruited in this study, with 48 patients recruited at each center.

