**Methods/Design:**

This is a multicenter, randomized, double-blind, placebo-controlled, phase II clinical trial. A total of 240 eligible patients will be recruited from five centers. Patients are randomly assigned to high-dose group, middle-dose group, low-dose group, or control group in a 1 : 1 : 1 : 1 ratio. All drugs are required to be taken 3 times daily for 5 days with a 5-day follow-up period. Primary outcomes are duration of all symptoms, total score reduction on Jackson's scale, and TCM symptoms scale. Secondary outcomes include every single TCM symptom duration and score reduction, TCM main symptoms disappearance rate, curative effects, and comparison between Jackson's scale and TCM symptom scale.

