### 2.4. Randomization and Blinding

According to a stratified block randomization method, the PRCO PLAN function of the analysis system of SAS software (SAS Institute, Inc., Cary, NC, USA) was used to generate the random number grouping table according to the number of cases and the random proportion of the participating units. There are 5 centers and 4 groups (high-dose group, middle-dose group, low-dose group, and control group), and each group is divided into two layers in a 1 : 1 ratio, while one layer is aged between 45 and 60 years and the other layer is aged between 61 and 75 years. So each group in one single center will recruit 12 patients, with 6 patients between 45 and 60 years old and 6 patients between 61 and 75 years old. Eligible patients are randomly allocated to the high-dose group, middle-dose group, low-dose group, or control group in a 1 : 1 : 1 : 1 ratio. The randomization sequence was generated by the Health Statistics Department of the Fourth Military Medical University of China, which is independent of the trial. The details of randomization sequences are unknown to researchers and outcome assessors who participate in the study and kept in two copies in an opaque, sealed, and stapled envelope that will be kept concealed until the end of the outcome assessment.

The blinding codes are preserved and protected separately by West China Hospital and the other four participating centers. Emergency letters are prepared by a statistician in which the random code and group assignment are included. If the blind code is exposed, the corresponding patient will be excluded. Any of the following situations could call for a blind breaking and urgent measure: a serious adverse event, serious complication, or deteriorative condition.

Following the blinding principle, the five participating centers are isolated from the sponsor unit during the study and they will contact only the supervision agency (Beijing Chuangli Medical Technology Development Co., Ltd., China), which is responsible for contacting participating centers and monitoring the progress of research but is blind to group assignment.

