### 2.8. Statistical Analysis

The full analysis set (FAS) is the primary analysis set for efficacy with an intention-to-treat (ITT) principle. In the FAS, all patients will be treated with at least one dose of the study drug and at least one clinical observation will be recorded in the study. All subjects without any major protocol deviations will be involved in the per-protocol set (PPS). The safety analysis will be conducted for randomized subjects who have completed at least one study visit and have safety data. Descriptive statistics will be performed on continuous variables, frequencies, and categorical variables. All symptom durations, total score reductions on Jackson's scale and TCM symptoms, the duration of each TCM symptom, the decreasing rate of TCM main symptoms, and the reduction score of TCM symptoms will be estimated with the Kaplan-Meier technique and compared using the stratified log-rank test. Comparisons among different dose groups and age layers will be conducted with an analysis of variance (ANOVA) and a least significant difference *t*-test. In this multicenter trial, the Cochran-Mantel-Haenszel test stratified by clinical centers and the logistic regression model adjusted for covariates will be used. Statistical analyses will be conducted by an independent statistician from the Health Statistics Department of the Fourth Military Medical University using the SAS statistical software 9.1.3 (SAS, Cary, North Carolina State University, North Carolina, USA).

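### Sixty per group keeps 50 evaluable only up to a 16.7% loss, not the 20% stated; a 20% loss would need 63 per group (minor)

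*Protocol article*

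**What the plan says.** Section 2.3 (Sample Size Calculation) of the protocol article says that the number was determined by software "with 90% power and a significance level of 0.05 (two-sided"). Citing a published study, it states that "the sample size should consist of 50 participants in each group". It then goes from 50 to 60: "Considering the potential 20% loss, 60 participants are needed for each group". With four groups and five centers, "a total of 240 participants will be recruited in this study, with 48 patients recruited at each center".

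The section gives no outcome, effect size, standard deviation, event rate or comparison for the 90%. Elsewhere the article sets four equal groups (section 2.4) and three primary outcomes (Abstract and section 2.6.5). On the analysis population, section 2.8 says: "The full analysis set (FAS) is the primary analysis set for efficacy with an intention-to-treat (ITT) principle".

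**The concern.** A loss rate is a fraction of the people enrolled. To finish with 50 after losing a fifth, the target must be divided by 0.80. Multiplying by 1.20 always gives too few. Here the printed 60 does not do what its sentence says, and the error carries into the total of 240, the 48 per center, and the 12 per group per center in section 2.4.

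At stake is whether the stated power can be relied on at the loss rate the plan itself allows for. The trial is meant to find the optimal dose, so readers will judge a dose arm that shows no difference from control against the printed 90%. The sentence supporting that figure should therefore be arithmetically correct, and it should be clear what the figure refers to.

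**Working it through.** **Inputs.** From section 2.3: 50 evaluable per group, 20% loss, 60 enrolled per group, 240 in total, 90% power, two-sided 0.05. From section 2.4: four groups, 1:1:1:1. Not given: the outcome, effect, variability and comparison behind the 50.

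**Step 1: reproduce the plan's figure.**
- 50 × (1 + 0.20) = 60 per group
- 60 × 4 = 240 in total
- 240 / 5 = 48 per center

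The printed figures are reproduced exactly by the multiplication. (The 48 per center only happens to equal the 48 evaluable per group in step 3.)

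**Step 2: the number that a 20% loss needs.**
- N × (1 − 0.20) = 50, so N = 50 / 0.80 = 62.5, rounded up to 63 per group
- 63 × 4 = 252 in total
- Check: 63 × 0.80 = 50.4, which is at least 50

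**Step 3: what 60 provides.**
- 60 × 0.80 = 48 evaluable per group, two short of 50
- Largest loss that still leaves 50: 1 − 50/60 = 16.7%

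**Step 4: effect on power.** This needs an assumption, because the powered comparison is not stated. Assume a two-sample comparison of means, with 50 per group giving exactly 90% power at two-sided 0.05. By the normal approximation, the expected test statistic at 50 per group is 1.960 + 1.282 = 3.242, and it scales with the square root of the group size.
- At 48: 3.242 × √(48/50) = 3.176; 3.176 − 1.960 = 1.216; power = Φ(1.216) = 88.8%
- At 60 (no loss from the analysis): 3.242 × √(60/50) = 3.551; 3.551 − 1.960 = 1.591; power = Φ(1.591) = 94.4%

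The t-test version also gives 88.8% at 48. The effect size cancels out of this calculation. The value implied by 50 per group (about 0.65 SD on these assumptions) is a back-calculation and not a figure from the plan.

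**The case against.** **The shortfall hardly matters.** Two participants per group cost 90.0 − 88.8 = 1.2 points of power, and only if every lost participant leaves the primary analysis. Section 2.8 makes the full analysis set primary and asks only for one dose and one clinical observation. Section 2.2.4 keeps patients withdrawn for reasons such as allergy, serious adverse events or lack of improvement in that set. The number analysed may therefore exceed 48. This stands and is why the point is minor. It does not make the printed sentence correct.

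**The 20% might be meant relative to completers.** On that reading 50 × 1.2 would be right. But the text speaks of a loss, which is naturally a share of those enrolled, and nothing in section 2.3 suggests another base.

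**A stronger reading is tempting.** A reader might infer that the 90% holds only for a single two-group comparison, and that power is clearly lower for a trial with three doses and three primary outcomes ("Primary outcomes are duration of all symptoms, total score reduction on Jackson's scale, and TCM symptoms scale"). The document does not support this. Section 2.3 names no comparison, so what the 90% covers is unknown rather than known to be one pair of groups. Nor does lower power follow. The only procedure named for comparing dose groups is unadjusted ("Comparisons among different dose groups and age layers will be conducted with an analysis of variance (ANOVA) and a least significant difference" *t*-test), and with unadjusted tests each comparison keeps its own power. Power would fall under a multiplicity adjustment, or under a rule that all doses or all outcomes must succeed, but neither is stated. If one unadjusted success among several were enough, power would rise and the concern would be false positives, which is a different point. A statistical analysis plan that is not shown may settle these rules.

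A reader might also discount the power because the placebo contains 10% of the study drug. That would require knowing the shape of the dose response and whether the planning effect was set against an inert control. The article gives neither.

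**Conclusion.** The inflation for loss is wrong as printed. Sixty per group covers a loss of up to 16.7%; a 20% loss leaves 48, and 63 per group (252 in total) would be needed to keep 50. This follows from section 2.3 alone and needs no assumption beyond reading the loss as a share of those enrolled.

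The consequence is minor: about 89% power instead of 90% for one comparison, if the calculation was a two-sample comparison of means and all lost patients drop out of the analysis. The more withdrawn patients contribute data through the full analysis set, the smaller the drop. Whether the 90% itself is right for any primary outcome or dose-versus-control comparison cannot be checked from the article. That is a reason to ask the sponsor to say what it refers to, and not evidence that power is substantially lower.

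**What to change.** Keep 240 patients and restate section 2.3, for example: *Sixty participants per group allow for a loss of up to 16.7% while keeping 50 evaluable. With a 20% loss, 48 per group remain, and power for [dose-versus-control comparison] on [primary outcome], at an effect of [planned value], is [value].* The sponsor should fill the brackets from its own calculation. The figure of about 89% is a guide to what to expect if that calculation was a two-sample comparison of means. Neither the back-calculated effect nor a multiplicity method absent from the article should be written in on the strength of this review. The restatement should also say whether the 20% means patients missing from the full analysis set or patients who stop early but are still analysed.

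The cost is rewording, a slightly less favourable power statement, and no extra patients. Raising enrolment instead would be out of proportion. Section 2.4 splits each group equally over 5 centers × 2 age layers = 10 cells, so equal cells need group sizes in multiples of 10. The next size at or above 63 is 70 per group, or 280 in total: 40 more patients to address a shortfall worth about one point of power.

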### 2.4. Randomization and Blinding

According to a stratified block randomization method, the PRCO PLAN function of the analysis system of SAS software (SAS Institute, Inc., Cary, NC, USA) was used to generate the random number grouping table according to the number of cases and the random proportion of the participating units. There are 5 centers and 4 groups (high-dose group, middle-dose group, low-dose group, and control group), and each group is divided into two layers in a 1 : 1 ratio, while one layer is aged between 45 and 60 years and the other layer is aged between 61 and 75 years. So each group in one single center will recruit 12 patients, with 6 patients between 45 and 60 years old and 6 patients between 61 and 75 years old. Eligible patients are randomly allocated to the high-dose group, middle-dose group, low-dose group, or control group in a 1 : 1 : 1 : 1 ratio. The randomization sequence was generated by the Health Statistics Department of the Fourth Military Medical University of China, which is independent of the trial. The details of randomization sequences are unknown to researchers and outcome assessors who participate in the study and kept in two copies in an opaque, sealed, and stapled envelope that will be kept concealed until the end of the outcome assessment.

The blinding codes are preserved and protected separately by West China Hospital and the other four participating centers. Emergency letters are prepared by a statistician in which the random code and group assignment are included. If the blind code is exposed, the corresponding patient will be excluded. Any of the following situations could call for a blind breaking and urgent measure: a serious adverse event, serious complication, or deteriorative condition.

Following the blinding principle, the five participating centers are isolated from the sponsor unit during the study and they will contact only the supervision agency (Beijing Chuangli Medical Technology Development Co., Ltd., China), which is responsible for contacting participating centers and monitoring the progress of research but is blind to group assignment.

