#### 2.2.4. Withdrawal and Dropout

The study participation will be terminated if the amount of study medication taken is poor (actual usage of trial drug <80% or =120%) or the participant is unable to cooperate with the trial investigators and/or unable to complete the follow-up. When an allergic reaction or a serious adverse event is revealed, a participant is unwilling to continue the trial, or symptoms do not improve or worsen after taking the study drugs for 72 hours, the patient will be withdrawn from the trial after a researcher's assessment, and the data will be considered invalid but will be included in the full analysis set (FAS). If the participant drops out, he or she will be contacted via phone interviews, e-mail, or written letters. The reason for study discontinuation and the last time the medication was taken will be recorded. Participants who exit the trial due to allergies, poor curative effects, or other adverse events will receive appropriate treatment.

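### The rule that a patient whose code is exposed is excluded names no analysis set and, as written, contradicts the FAS and intention-to-treat statements for patients with serious events or deterioration

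*Protocol article*

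**What the plan says.** Four statements in the protocol article bear on this.

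- **Section 2.4 (Randomization and Blinding), consequence of a code break:** "If the blind code is exposed, the corresponding patient will be excluded". No analysis set is named and no exception is given.
- **Section 2.4, grounds for a code break:** "Any of the following situations could call for a blind breaking and urgent measure: a serious adverse event, serious complication, or deteriorative condition".
- **Section 2.2.4 (Withdrawal and Dropout):** for patients withdrawn because of an allergic reaction, a serious adverse event, unwillingness to continue, or lack of improvement or worsening after 72 hours on drug, "the data will be considered invalid but will be included in the full analysis set (FAS".
- **Section 2.8 (Statistical Analysis):** "The full analysis set (FAS) is the primary analysis set for efficacy with an intention-to-treat (ITT) principle". FAS membership is described by dosing and observation only: "all patients will be treated with at least one dose of the study drug and at least one clinical observation will be recorded". For the per-protocol set: "All subjects without any major protocol deviations will be involved in the per-protocol set (PPS". For safety: "The safety analysis will be conducted for randomized subjects who have completed at least one study visit and have safety data". None of these definitions mentions unblinding.

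**The concern.** Exclusion after randomisation is harmless to a comparison only if it is unrelated to outcome. Here the grounds for opening the code are themselves bad outcomes, so an exclusion that follows a code break depends on how the patient fared. An intention-to-treat analysis is meant to prevent that.

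The practical problem is that one patient can fall under two opposite rules. A patient with a serious adverse event who is withdrawn and whose code is opened is kept in the FAS by section 2.2.4 and excluded by section 2.4. Which rule governs is left open, so membership of the primary efficacy set could be decided after the patient's outcome and treatment are known. In a four-arm dose-finding trial, a difference between arms in the number of such patients would carry straight into the dose comparison.

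**Working it through.** **1. The texts side by side.** The plan states no figure on this point, so the main check compares the wording.

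| Section | Patient concerned | What happens |
|---|---|---|
| 2.4 | Code exposed; possible grounds are a serious adverse event, serious complication or deterioration | Excluded; set not named |
| 2.2.4 | Withdrawn for a serious adverse event or worsening, among other reasons | Kept in the FAS |
| 2.8, FAS | Dosed at least once and observed at least once | In the primary efficacy set, intention-to-treat |
| 2.8, per-protocol set | No major protocol deviation | In the per-protocol set |
| 2.8, safety | Randomised, at least one visit, safety data | In the safety analysis |

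A dosed and observed patient with a serious adverse event and an opened code meets the FAS definition in 2.8 and the retention rule in 2.2.4, yet is excluded by 2.4. The three sections agree only if the exclusion in 2.4 is confined to the per-protocol set or means stopping participation. Section 2.4 says neither.

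**2. What would follow if the exclusion reached the FAS.** This is an illustration, not an estimate.

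Inputs:
- Group size 60, from section 2.3 ("Considering the potential 20% loss, 60 participants are needed for each group").
- Endpoint: the binary curative effect on day 11 (score reduction of at least 50%), a secondary outcome in section 2.6.6, chosen because its arithmetic is transparent.
- Assumed: equal true success in both arms, at 80% (48/60) or 70% (42/60).
- Assumed: k code-broken patients per arm, from 0 to 6, all failures.

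Formula: observed success after exclusion = s / (60 − k), where s is the number of successes.

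| Removed, arm A vs arm B | s = 48 | Difference (points) | s = 42 | Difference (points) |
|---|---|---|---|---|
| 3 vs 0 | 48/57 = 84.2% vs 48/60 = 80.0% | +4.2 | 42/57 = 73.7% vs 42/60 = 70.0% | +3.7 |
| 3 vs 1 | 48/57 = 84.2% vs 48/59 = 81.4% | +2.9 | 42/57 = 73.7% vs 42/59 = 71.2% | +2.5 |
| 6 vs 1 | 48/54 = 88.9% vs 48/59 = 81.4% | +7.5 | 42/54 = 77.8% vs 42/59 = 71.2% | +6.6 |
| 3 vs 3 | 48/57 = 84.2% in both | 0 | 42/57 = 73.7% in both | 0 |

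Differences are taken before rounding. The true difference is zero in every row. Within an arm, removing failures always raises the observed rate. Between arms, a spurious difference appears only when the numbers removed differ, and it favours whichever arm lost more patients. If these patients stay in the FAS, as 2.2.4 and 2.8 say, none of this arises.

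**3. Safety set.** In Table 3, Visit 1 includes the baseline safety tests as well as randomisation and drug distribution. A patient who is randomised at Visit 1 and never takes a dose therefore has one visit and safety data, and meets the definition in 2.8.

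**The case against.** The strongest reply is that section 2.4 concerns blinding and does not define analysis sets. The sections that do deal with analysis sets, 2.2.4 and 2.8, retain these patients, and being specific they should prevail; excluded may then mean taken out of the trial or out of the per-protocol set. That reading is possible, and it is why the point is a contradiction to be resolved and not proof that data will be lost. It does not dispose of the point. The sentence is mandatory and unqualified, and where 2.2.4 speaks of withdrawal it adds that the data stay in the FAS, which 2.4 does not. Nor is this detail left to a fuller protocol or analysis plan: it is a stated rule that conflicts with other stated rules.

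A reader might infer several stronger things that the documents do not support:

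- **That the worst outcomes are removed.** The grounds for a code break are permissive, so not every serious event or deterioration opens the code, and 2.2.4 expressly keeps such withdrawals in the FAS.
- **That serious harms disappear from the safety results**, for example 3 of 60 becoming 0 of 57. The safety definition has no unblinding exclusion, and section 2.7 requires adverse events to be recorded and severe ones reported within 24 hours.
- **That the bias favours the drug.** If more control patients deteriorated and were excluded, it would run against the drug; with equal true rates and equal numbers excluded, the difference is unaffected.
- **That the safety definition drops a dosed patient who leaves early.** It does not require post-dose data, and Visit 1 is a study visit with safety tests, so on a literal reading that patient is kept.

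**Conclusion.** The concern stands as an unresolved contradiction between section 2.4 and sections 2.2.4 and 2.8 over who belongs in the primary efficacy set. It matters because the exclusion depends on outcome events after randomisation and could, if applied to the FAS or safety set, bias dose comparisons when code breaks are unequal across arms.

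Neither the size nor the direction of any bias can be computed, since the protocol gives no code-break rate. The spurious differences of 2.5 to 7.5 points shown above rest on assumed success rates of 70% or 80%, assumed unequal removals of 3 vs 0, 3 vs 1 and 6 vs 1, and the assumption that every removed patient is a failure. They show only what a few unequal exclusions could do in arms of 60.

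The safety-set point is secondary and minor: the definition can count a randomised patient who was never dosed.

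**What to change.** Replace the exclusion sentence in section 2.4 with: *Unblinding is recorded as a protocol deviation; the patient stays in the FAS and the safety set with all data, and may be excluded only from the PPS.* Sections 2.2.4, 2.4 and 2.8 then agree. The change leaves the grounds for breaking the code as they are.

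As a minor companion change in section 2.8, define the safety set as all randomised patients who took at least one dose.

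The cost is one sentence for the main point and one for the safety set, with no extra patients or data. Both should be settled before treatment codes are opened for analysis.
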